### Post-Treatment Assessment and Follow-Ups

Once treatment is finished, we invite all participants to a post-treatment assessment. Over the following 12 months we invite them to attend research assessments at three, six, nine and twelve months after treatment. We also invite those allocated to treatment with MBCT or CPE to attend two treatment sessions, one 6-8 weeks, the other six months after treatment. At post-treatment assessment (T1), we use the SCID mood disorder module to assess current diagnostic status and any changes in that status over the treatment phase. We ask participants to repeat the cognitive tasks and questionnaires they completed during the pre-treatment assessments with the exception of the Childhood Trauma Questionnaire (CTQ), the worst ever BSS, the crisis card, and questions about sociodemographic status. The follow up assessments at three (T2), six (T3) and nine months (T4) consist of a SCID mood disorder module, the Hamilton Rating Scale for Depression and, when there has been suicidal behaviour or self harm, the SASII assessment, focusing on the time since the last assessment. We also ask them to complete questionnaires assessing current symptoms and history of treatment since last assessment (BSS current, Suicide Cognitions Questionnaire, MINI Suicidality Tracking, BDI-II, BHS, Life Events Questionnaire, CORE, Euro-QOL, PHQ9, GAD7). During the final follow-up assessment (T5), we ask participants to complete the same measures as at the T1 assessment. Additional File 1 includes a table summarizing all these baseline and follow-up assessments.

### Withdrawal

Participants can withdraw from treatment or data collection or both at any time without having to give a reason. Nevertheless we ask those who withdraw from the trial treatment (MBCT or CPE) to attend all the remaining research appointments or at least to provide minimal data if they are willing.

### Safety monitoring and reporting

We record and report suspected serious adverse events to the Trial Steering Committee (TSC), the Data Monitoring and Ethics Committee (DMEC), and serious adverse reactions to the Multi-centre Research Ethic Committee according to their individual guidelines.

### Analysis

We shall analyse all data by intention to treat. We shall use Cox regression, a form of survival analysis that takes account of covariates, to analyse relapse and recurrence. We shall analyse most other measured variables by mixed-model analysis of variance (ANOVA). We shall use baseline values of the dependent variable as a covariate in all analyses; we shall use other baseline measures or demographic characteristics as covariates when they contribute significantly to the analysis. We shall use multi-level modeling to take account of the clustering of participants within classes within centres. To minimise testing, we shall combine measured outcomes at different time points using the 'area under (the resulting) curve'. We shall use cognitive measures to explore the extent to which they mediate relapse and recurrence during treatment and follow up. Similarly we shall use data at each time-point on the Beck Scale for Suicide Ideation to explore the extent to which the cognitive measures mediate the occurrence of suicidality over the follow-up period, again analysing 'area under the curve'. Additionally we shall examine recurrence of suicidality specifically for those participants who relapse to Major Depression (MDD) and had a history of suicidal ideation or behaviour at entry to the trial. We predict that, all else being equal, suicidal ideation will fall in those who have received treatment with MBCT. Further details of the data analysis plans are given in Appendix 1.

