## Methods/Design

This is a multi-centre, randomised controlled trial. We randomise participants between Mindfulness-Based Cognitive Therapy (MBCT) in addition to Treatment As Usual (TAU), Cognitive Psycho-Education (CPE) in addition to TAU, and TAU alone. In doing so, we stratify participants by (a) research centre (Oxford or Bangor) (b) cohort (c) history of suicidality (none, ideation or suicidal attempt) and (d) whether or not they were taking antidepressants in the 7 days before their first assessment. We originally proposed to stratify by centre, cohort, suicidal behaviour (ideation versus attempt), number of previous episodes of depression (3 or 4 versus 5 or more), and brooding (high versus low scores on a subscale of the Ruminative Response Style questionnaire). However we later changed these, with ethical approval, to reflect the inclusion of participants taking antidepressants or without suicidal ideation. We undertake randomisation by e-mail to the remote randomisation centre at the North Wales Organisation for Randomised Trials in Health (NWORTH) at Bangor University. The randomisation algorithm uses dynamic allocation to protect against subversion while ensuring that each arm of the trial is comparable with respect to the stratification variables. For validation the randomisation e-mail also includes additional information including the participant's date of birth, gender and date of assessment.

We monitor treatment effects over a period of one year. Assessments by trained assessors who are blind to treatment allocation (and whose blindness is checked within each assessment session) take place directly before and after the start of the treatment (T0 and T1), and at three (T2), six (T3), nine (T4) and twelve months (T5) after T1 (see Figure 1 for details of participant flow through the trial). We also offer treatment 'reunions' to participants in both MBCT and CPE at both 6-8 weeks and 6 months after treatment.

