The intention in this trial is to examine MBCT for people with severe recurrent depression, including suicidal ideation or behaviour. We considered including only participants who at the outset acknowledge experience of suicide ideation or behaviour. However the stigma associated with suicidality and the frequent failure to disclose suicidal thoughts and behaviours to clinical staff, made us suspicious that this would reduce recruitment to the trial. For example consultation with GP practices revealed reluctance to circulate information about a trial explicitly targeting suicidal depression to patients whose practice notes might not record such a history. We were also concerned that people would be less likely to refer themselves to the trial if posters and other material focused on suicidal ideation or behaviour. Although the stigma surrounding suicidal ideation and behaviour is unfortunate and should be challenged, recruitment is crucial in trials. So, although the special interest in suicidal depression is shared with referring clinicians, recruitment is open to all who have experienced recurrent depression, rather than specifying minimum levels of suicidality as an inclusion criterion. We then stratify participants according to history of suicidality reported on standardised measures used in the initial assessments of eligibility, and use these measures as covariates in the definitive analysis. We still expect most participants to report some history of suicide ideation or behaviour, even though this is not explicit in recruitment materials.

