## Appendix 1: Statistical Analysis Plan

The primary outcome measure will be the time to relapse or recurrence meeting DSM-IV criteria for a major depressive episode (American Psychiatric Association, 1994) on the Structured Clinical Interview for DSM-IV (SCID, Spitzer et al., 1992). Occurrence of relapse or recurrence will be assessed after treatment (T1), and at three (T2), six (T3), nine (T4) and twelve (T5) months thereafter by trained psychologists blind to participants' treatment condition. If the interview establishes that symptoms meeting diagnostic criteria for major depression have been present since the last assessment, we shall ask participants when this episode of depression started (and ended, if they are no longer symptomatic). 'Return to treatment' will also be treated as a relapse or recurrence if, in the judgment of a blind rater, the participant experienced exacerbation of their symptoms that would have met the criteria for Major Depression in the absence of immediate treatment.

The analysis will be by 'intention to treat' (ITT). The time (in weeks) of relapse or recurrence to Major Depression, as defined above, will be the dependent variable in survival analysis. The treatment group and stratification variables will be used as predictors.

For participants who are lost from the trial we shall use their available measures and then censor them at the time of their last observation. Since only a participant's first relapse or recurrence to Major Depression will contribute to the survival analysis, the subsequent loss of that participant will not affect the analysis.

Participants who miss one or more follow-up assessments, but are then assessed at a later time point will be asked whether they have experienced a relapse or recurrence according to SCID diagnostic criteria since the last assessment, including time periods which would have been covered in missed assessments. This will enable us to assess the time to relapse and thus to censoring.

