We shall use the clinician-rated Hamilton Rating Scale for Depression (HRSD, to assess severity of depression at all time points. We shall follow De Rubeis et al. (2005) and Hollon et al (2005) in using a score of 14 or more on the HRSD to indicate relapse, thus complementing the SCID diagnosis. HRSD scores also provide a quantitative measure of outcome that strengthens the dichotomised outcome of diagnosis, because, as a quasi-continuous measure, it has more power to detect differences between groups.

The other quantitative measures used at baseline, before treatment, and at times T1 to T5 are the Beck Depression Inventory (BDI-II), Beck Hopelessness Scale (BHS), Beck Scale for Suicide Ideation (BSS current) and the EQ5D. We shall calculate the 'area under the curve' (AUC) of each measure to give a single score. For the EQ5D this is known as a QALY.

Missing items within individual outcome measures will be treated according to the instructions for that measure. If two or more observations for quantitative measures are available between T1 and T5, then we shall use linear regression to estimate the missing values and the AUC. If there is only one observation available between T1 and T5 then we shall estimate the remaining values from the general slope estimated from all participants with two or more observations. If no observations for T1 to T5 are available then the AUC is also missing. If the trend among participants with full data departs from linear, then we shall use the observed trend to estimate the missing values.

For the quantitative measures we shall use a mixed-model analysis of covariance (AnCova). We shall use baseline measures as covariates, and multi-level modeling to take account of the clustering of participants within classes within centres. As covariates we shall also use the stratification variables and treatment group, together with the number of sessions attended and, in the MBCT group, number of hours of home practice. These will allow us to estimate how the response to the two treatments depends on their 'dose'.

Potential moderators to be examined include gender, residual symptoms of depression (e.g. HRSD score and BDI-II score at baseline) and stability of remission, course of previous history (chronic vs episodic), and age of onset.

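### The rule that adds covariates when they are significant leaves the primary Cox model open to outcome-driven choice and does not match the fixed covariate sets in Appendix 1

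*Protocol article*

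**What the plan says.** All of this is in the protocol article.

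- Analysis, primary method: "We shall use Cox regression, a form of survival analysis that takes account of covariates, to analyse relapse and recurrence". The next sentence assigns most other measured variables to mixed-model ANOVA.
- Analysis, covariates: "We shall use baseline values of the dependent variable as a covariate in all analyses", and then, in the same sentence, "we shall use other baseline measures or demographic characteristics as covariates when they contribute significantly to the analysis".
- Analysis, closing pointer: "Further details of the data analysis plans are given in Appendix 1".
- Appendix 1, survival model: "The treatment group and stratification variables will be used as predictors". Methods/Design lists those variables: "we stratify participants by (a) research centre (Oxford or Bangor) (b) cohort (c) history of suicidality (none, ideation or suicidal attempt"), and (d) antidepressant use in the week before first assessment.
- Appendix 1, quantitative measures: baseline measures are covariates, and "As covariates we shall also use the stratification variables and treatment group, together with the number of sessions attended", plus hours of home practice in the MBCT group. No significance test decides entry.
- Discussion, on the measures of suicidality history: "use these measures as covariates in the definitive analysis". No condition is attached.

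**The concern.** The rule is stated, not left open for a later document. As worded it covers every analysis, so the covariates in the primary model would be settled by the same data that give the treatment effect. The section on eligibility and baseline measures lists more than 20 instruments and tasks besides demographics, so the pool is large. Two analysts could follow the sentence faithfully and report different primary hazard ratios.

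Three things are at stake. First, standard errors reported after selection ignore the selection. Second, a hazard ratio is non-collapsible: when there is a treatment effect, changing the covariate set changes the quantity being estimated. Third, the MBCT versus CPE comparison is planned at 80% power, so a modest shift in the estimate could decide a borderline result.

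**Working it through.** **Step 1. The plan's own figures.** Inputs from Sample Size: 120 MBCT, 120 CPE, 60 TAU; relapse 39%, 57% and 70%; 5% significance, taken here as two-sided. HR = ln(1 − p1)/ln(1 − p2); events E = sum of n × p; Freedman power = Φ(√(E·r)·(1 − HR)/(1 + r·HR) − 1.96), where r is the MBCT:comparator ratio.

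- MBCT v CPE: HR = ln 0.61/ln 0.43 = 0.586; E = 46.8 + 68.4 = 115.2; r = 1; power 80.1% (stated: 80%).
- MBCT v TAU: HR = ln 0.61/ln 0.30 = 0.411; E = 46.8 + 42.0 = 88.8; r = 2; power 99.1% (stated: 99%).
- Recruitment: 300/(1 − 0.20) = 375 (stated: 375).

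All three reproduce without any covariate adjustment, so they do not depend on the rule.

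**Step 2. The passages side by side.**

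| Model | Analysis section | Appendix 1 |
|---|---|---|
| Time to relapse (Cox) | baseline value of the outcome, plus whatever is significant | treatment and stratification variables |
| Quantitative measures | baseline value, plus whatever is significant | baseline, treatment, stratification variables, attendance, home practice |

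Inclusion criterion 3 requires recovery or remission at baseline, so time to relapse has no baseline value. For the Cox model, the first half of the covariate sentence is therefore empty and only the significance rule is left.

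**Step 3. Size of the effect under no treatment difference.** Assumptions, none of them in the documents: independent normal candidates; 0 or 5 of them prognostic (0.2 log-HR or 0.2 SD each); kept at p<0.05, either one at a time or by backward elimination. There are 120 per arm, with about 48% events in the Cox runs, the mean of 39% and 57%. Entries are type I error in %.

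| Model, candidates/prognostic, method (replicates) | Treatment only | Selected | Better of the two |
|---|---|---|---|
| Cox, 10/0, one at a time (3,000) | 4.6 | 5.0 | 5.2 |
| Cox, 10/0, backward (3,000) | 5.7 | 5.9 | 6.1 |
| Cox, 10/5, one at a time (3,000) | 5.0 | 5.8 | 7.1 |
| Cox, 10/5, backward (3,000) | 4.5 | 5.9 | 7.0 |
| Cox, 10/5, one at a time (5,000) | 4.8 | 5.7 | 6.7 |
| Cox, 20/0, one at a time (3,000) | 5.0 | 5.8 | 6.2 |
| Linear, 10/0, one at a time (6,000) | 5.0 | 5.1 | 5.3 |
| Linear, 10/0, backward (6,000) | 5.0 | 5.2 | 5.4 |
| Linear, 10/5, one at a time (6,000) | 4.7 | 5.3 | 7.1 |
| Linear, 10/5, backward (6,000) | 4.7 | 5.5 | 7.2 |

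Simulation error is √(0.05 × 0.95/replicates): about 0.4 points at 3,000 and 0.3 at 5,000 or 6,000. The excess of selected over treatment-only is 0.1 to 1.5 points. It passes one point in a single row, where the treatment-only figure itself fell to 4.5%. A Cox model with all 10 covariates fixed in advance gave 5.3% in 5,000 runs, against 5.7% with selection; that difference is within simulation error.

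**Step 4. Larger pools, unequal arms and discretion (linear model, 5 weakly prognostic covariates).**

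- With 30 candidates, one run of 3,000 gave 6.5% (fixed set 5.5%). Runs of 12,000 with treatment in the model gave 5.4% to 5.8%, and 5.2% to 5.3% with 20 candidates. Screening covariates without treatment in the model gave 5.0% and 4.9% with 20 and 30 candidates (20,000 runs), so no inflation.
- With 20 candidates, correlation 0 or 0.3 and 4,000 runs, three procedures were tried that the sentence would allow: one at a time at p<0.05, and backward at p<0.05 and at p<0.10.

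| Arms | One procedure | Best of three | Also allowing unadjusted |
|---|---|---|---|
| 120 v 120 | 4.8–6.0% | 5.7–6.9% | 7.4–9.0% |
| 120 v 60 | 4.9–6.5% | 7.2–7.5% | 8.8–9.7% |

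Fixed covariates in the same setting gave 4.5% to 5.8%. Between procedures the treatment estimate moved by a median of 0.12 to 0.23 SE.

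**The case against.** The strongest reply is that the Analysis section is a summary that defers to Appendix 1, and Appendix 1 already names a set for each model. The disputed sentence follows the ANOVA sentence and opens with a clause that cannot fit time to relapse, so it may have been written for the measured outcomes only. This has weight: the scope is ambiguous. But the sentence says all analyses and exempts none, and Appendix 1 neither repeats nor limits the rule. The text does not let a reader settle which model is primary.

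A reader might infer a flat contradiction. The documents do not support that: Appendix 1 does not say that its predictors are the only ones. What stands is an open rule beside a fixed list.

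A reader might also infer that the tests are materially too liberal. The simulations do not support that for a rule applied mechanically; one plausible way of screening gives no inflation at all.

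Lastly, a reader might call it an error that the Cox model has no fixed symptom covariate. That is a preference. Appendix 1 gives baseline HRSD and BDI-II a role as moderators, and nothing in the document shows how strongly they, or the number of previous episodes, predict relapse.

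**Conclusion.** The concern holds in a limited form. The significance rule does not match the named sets in Appendix 1, and as worded it keeps the primary Cox model from being fixed before the outcomes are seen. The clause on baseline values in all analyses cannot work for the primary outcome.

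The size is small if one procedure is applied mechanically: about 5.0% to 5.9% type I error in the main runs, generally less than one point above a fixed model. Figures of about 7% or more need the added assumption that the analyst picks among results. They bound what discretion could do and do not predict conduct. All these figures rest on assumed candidate numbers, prognostic strength and thresholds, and the 120 v 60 comparison was simulated only in a linear model. The case for change therefore rests mainly on having one identifiable primary hazard ratio, and less on error inflation. This is a free improvement.

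**What to change.** 1. Delete the significance rule from the Analysis section.
2. State that the primary Cox model contains treatment group and the stratification variables, as in Appendix 1, and nothing else.
3. Restrict the baseline-value clause to the quantitative outcomes, and use treatment, stratification variables and the baseline value there. Attendance and home practice arise after randomisation and serve the dose question in Appendix 1, so they belong in a separate dose model.
4. Label any model with other covariates a sensitivity analysis.

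Adding baseline HRSD or BDI-II to the primary model is optional, provided it is fixed before unblinding.

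The cost is wording only. No new data are needed, and the 375 to be recruited, the final 300 and the stated powers are unchanged.

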Recurrence of suicidal ideation, both within episodes of major depression and over the follow-up period, is an important secondary outcome. Initially we shall examine recurrence of suicidality specifically for those participants who relapse to Major Depression and had a history of suicidal ideation or behaviour at entry to the trial. Then we shall compare severity of suicidal symptoms, as measured by the Beck Scale for Suicide Ideation (BSS current) and the MINI suicide-tracking measure, across the follow-up period for all participants, whether or not they relapsed or became suicidal. Finally we shall compare suicidal cognitions (and ability to let go of cognitions that occur), at baseline, T1 and T5 only between groups using AnCova, with T0 as covariate and T1 and T5 as separate outcomes.

By assessing cognitive measures relevant to risk of relapse to depression, namely mindfulness, suppression, self-compassion, rumination, self guides, autobiographical memory and executive capacity, before and immediately after treatment and at the end of follow-up, we can use them in an explanatory analysis to study factors that mediate efficacy. We shall use regression analysis (binary logistic regression for the dichotomous outcome of relapse and linear regression for the worst HRSD score during follow-up) to explore whether the change from T0 to T1 in each of these measures can account for the effects of treatment on risk of relapse.

Where necessary we shall transform variables closer to Normal distributions for AnCova. Where data are missing, we shall use data from alternative sources, notably therapists on the trial and referring general practitioners. We shall also use sensitivity analysis to assess the effect of including participants whose data on relapse is collected by these means.

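### The mediation analysis lets relapses that began before T1 count as outcomes of a mediator measured at T1, so part of any mediator-relapse association may run backwards

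*Protocol article*

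**What the plan says.** The point rests on several places in the protocol article, read together.

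- **Outcome window.** The Analysis section states: "We shall use cognitive measures to explore the extent to which they mediate relapse and recurrence during treatment and follow up".
- **Mediator.** Appendix 1 asks "whether the change from T0 to T1 in each of these measures can account for the effects of treatment on risk of relapse".
- **Model.** Appendix 1 names "binary logistic regression for the dichotomous outcome of relapse and linear regression for the worst HRSD score during follow-up". The relapse model is yes/no, and no start date for counting relapses is given.
- **Timing of the measures.** Appendix 1 has them taken "before and immediately after treatment and at the end of follow-up, we can use them in an explanatory analysis to study factors that mediate efficacy". The second of these times is T1, after the eight weekly classes.
- **Treatment-phase relapses count.** Appendix 1: "Occurrence of relapse or recurrence will be assessed after treatment (T1), and at three (T2), six (T3), nine (T4) and twelve (T5) months thereafter". The section on post-treatment assessment uses the SCID at T1 "to assess current diagnostic status and any changes in that status over the treatment phase".
- **Suicidal ideation.** The Analysis section also explores mediation of suicidality through the area under the curve of the Beck Scale for Suicide Ideation (BSS). The rules in Appendix 1 for estimating that area work on observations from T1 to T5.

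**The concern.** A mediator has to come before the outcome it explains. For a relapse that began during the classes, the T1 score comes afterwards. A participant who is in an episode at T1, or has just had one, may well report more rumination and less mindfulness or self-compassion because of it. The yes/no relapse variable cannot tell these cases from relapses that followed T1, so a backward association enters the mediator-relapse path.

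The other path, from arm to mediator, may exist whether or not it protects against relapse, because MBCT trains some of the measured skills directly. If both paths appear, the result looks like a mechanism. Mediators of outcome are part of the objectives, and the Discussion intends to use findings on mechanism to refine the treatment, so a spurious mediator could misdirect that work.

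The BSS analysis has a milder form of the problem. If the mediator is again the change to T1, an area that starts at T1 includes an outcome score taken at the same visit as the mediator.

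**Working it through.** **Planning rates.** The Sample Size section gives relapse of 39% (MBCT), 57% (CPE) and 70% (TAU), with 120, 120 and 60 participants. As a check on these inputs for MBCT against CPE:

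- Hazard ratio = ln(0.61)/ln(0.43) = 0.586.
- Events = 120 × 0.39 + 120 × 0.57 = 115.2.
- Power at two-sided 5% = Φ(√(115.2/4) × |ln 0.586| − 1.96) = 81.9% by Schoenfeld's formula, or 80.1% by two proportions.

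The stated 80% reproduces. It is background only; nothing in this point disputes it.

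**Relapses before T1.** The document gives no figure. Assume a constant hazard over 2 months of treatment plus 12 months of follow-up, with the planning rates reached at month 14.

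| Arm | Monthly hazard | Relapse before T1 | Share of the arm's relapses |
|---|---|---|---|
| MBCT | −ln(0.61)/14 = 0.0353 | 1 − exp(−2 × 0.0353) = 6.8% | 0.068/0.39 = 17% |
| CPE | −ln(0.43)/14 = 0.0603 | 1 − exp(−2 × 0.0603) = 11.4% | 0.114/0.57 = 20% |

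In numbers, 120 × 0.068 + 120 × 0.114 ≈ 22 of about 115 relapses. Counting in weeks (8 + 52), with the planning rates reached at week 60 or at week 52, gives 16-17% for MBCT, 19-20% for CPE and 21-23% for TAU.

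**Effect on the mediation test.** Simulation with 120 per arm, the hazards above, a T0-T1 correlation of 0.6, and a mediator with no effect on relapse. MBCT shifts the T1 mediator by 0.5 to 0.8 SD. A relapse before T1 worsens the T1 score by the amount shown. Neither size is given in the document. The ranges cover both arm effects and repeated runs.

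| Worsening from early relapse | Both paths significant at 5% | False share of treatment effect accounted for |
|---|---|---|
| 0.5 SD | 10-13% | 8-13% |
| 1.0 SD | 32-33% | 15-24% |
| 1.5 SD | 53-60% | 20-33% |

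Restricting to participants relapse-free at T1 brings joint significance back to 4-6% and the share to 0%. Adjusting for the T0 score does not help: joint significance is then 13-14%, 33-36% and 65-67%.

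**Without an arm effect on the mediator.** Joint significance falls to about 1-4% and the false share to below 1%. The mediator-relapse path alone remains inflated. With a change score of unit SD it is significant in 7.8% of trials at 0.5 SD worsening and 24.3% at 1.0 SD, against 3.7% and 5.6% among those relapse-free at T1.

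**The case against.** The strongest reply is that no single sentence regresses pre-T1 relapse on the T1 change. The Analysis section gives the relapse window without a mediator time point, and Appendix 1 gives the time point without a window. That is true. But Appendix 1 is where the Analysis section sends the reader for detail, and nothing in either place limits the outcome to relapses after T1. Weekly ratings of rumination and thought suppression are collected during treatment and could support a time-ordered analysis, but the stated regression does not use them.

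The stakes are also limited. The analysis is exploratory, roughly 80% of relapses would have the right order under the constant-hazard assumption, and the main test of the meditation component is the randomised MBCT-CPE comparison. All of this stands.

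Two stronger readings are tempting and not supported:

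- **That the trial would report a mechanism that does not exist.** This needs both an arm effect on the mediator and a worsening of the T1 score after early relapse, and the document gives a size for neither. An arm effect is plausible for mindfulness. It is less clear for autobiographical memory or executive capacity, and CPE also teaches disengagement from rumination. The simulation gives every early relapser the full worsening at T1, although some episodes will have ended by then.
- **That the worst-HRSD model has the same fault.** It would only if T1 counted as follow-up. The section on post-treatment assessment keeps T1 apart from the follow-up visits T2 to T5, so that model already reads as T2-T5.

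**Conclusion.** The concern holds for the relapse mediation model and, in a milder same-visit form, for the BSS area under the curve. As written, the plan lets an outcome precede its supposed mediator. At the planning rates with constant hazard this affects about 17% of MBCT and 20% of CPE relapses.

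How much damage follows depends on assumptions. Given an MBCT effect of 0.5 to 0.8 SD on the mediator, false joint significance runs from roughly 11% to 60% as the worsening from an early relapse goes from 0.5 to 1.5 SD. Given no arm effect, it is about 1-4%, with the mediator-relapse path alone still inflated. The size is therefore conditional, but the fault in ordering is not. It deserves correction because mechanism is a stated aim. It does not touch the primary result.

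**What to change.** - Remove the reference to the treatment phase from the mediation sentence in the Analysis section, and state the same window in Appendix 1.
- In the relapse mediation model, include participants who are relapse-free at T1 and count only relapses with onset after T1. Appendix 1 already collects onset dates.
- In the mediation analysis of suicidal ideation, compute the BSS area under the curve over T2-T5.
- Leave the full-period intention-to-treat Cox analysis as it is.

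The change is to wording only; no new data are needed. The analysis loses about a fifth of relapses and becomes conditional on a post-randomisation state that treatment may affect, and the plan should say so. A time-ordered model using the weekly ratings, where those cover the mediator, could serve as an alternative or a sensitivity analysis.
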